## Abstract

**Background:**

Improper refractive correction can be harmful to eye health, aggravating the burden of vision impairment. During most optometry clinical consultations, practitioner-patient interactions play a key role. Maybe it is feasible for patients themselves to do something to get high-quality optometry. But the present empirical research on the quality improvement of eye care needs to be strengthened. The study aims to test the effect of the brief verbal intervention (BVI) through patients on the quality of optometry service.

**Methods:**

This study will take unannounced standardized patient (USP) with refractive error as the core research tool, both in measurement and intervention. The USP case and the checklist will be developed through a standard protocol and assessed for validity and reliability before its full use. USP will be trained to provide standardized responses during optical visits and receive baseline refraction by the skilled study optometrist who will be recruited within each site. A multi-arm parallel-group randomized trial will be used, with one common control and three intervention groups. The study will be performed in four cities, Guangzhou and three cities in Inner Mongolia, China. A total of 480 optometry service providers (OSPs) will be stratified and randomly selected and divided into four groups. The common control group will receive USP usual visits (without intervention), and three intervention groups will separately receive USP visits with three kinds of BVI on the patient side. A detailed outcome evaluation will include the optometry accuracy, optometry process, patient satisfaction, cost information and service time. Descriptive analysis will be performed for the survey results, and the difference in outcomes between interventions and control providers will be compared and statistically tested using generalized linear models (GLMs).

**Discussion:**

This research will help policymakers understand the current situation and influencing factors of refractive error care quality, and then implement precise policies; at the same time, explore short and easy interventions for patients to improve the quality of optometry service.

**Trial registration:**

Chinese Clinical Trial Registry ChiCTR2200062819. Registered on August 19, 2022.

**Supplementary Information:**

The online version contains supplementary material available at 10.1186/s12886-023-03023-y.

## Introduction

### Background

In 2019, an estimated 2.2 billion people worldwide were vision impaired, and at least 1 billion of them could have been prevented or cured [1]. Myopia is the predominant type of refractive error, and uncorrected refractive error is the leading cause of avoidable visual impairment worldwide [1, 2]. The incidence of myopia is increasing rapidly in China, which also has one of the largest numbers of patients with refractive error [2, 3]. Wearing spectacles provides a cost-effective way to correct refractive error, and optometry is an essential part of refractive correction [4]. However, they are prescribed or dispensed by a wide range of eye care providers, including primary eye care clinicians, ophthalmic personnel, optometrists, ophthalmologists, and personnel without any formal training or professional certification [5]. In addition, the optometry service and functions carried out by each eye care provider are largely dependent on the demand for services and financial incentives in different kinds of eye care facilities, potentially compromising the quality of eye care [6].

Global health faces enormous challenges in providing high-quality eye care in low and middle-income countries [1, 7, 8]. Uncorrected or improperly corrected refractive errors greatly affect patients’ health and quality of life, and even bring a huge economic burden to society [9]. Despite the potential negative effects of poor eye care, few researchers have conducted research on this issue in China. A few studies have discovered a high rate of inaccuracy of spectacle prescriptions. Nearly half (48.8%) of children in rural Guangdong with glasses had an absolute difference in prescription by ≥ 1.00D and 17.7% by ≥ 2.00D [10]. Among children who received optometry in rural western China, 9.1% had poor vision due to inappropriate refractive correction [11]. This study also suggested that rural optometrists were overly dependent on computerized optometry and could not effectively improve vision with subjective optometry. A survey in Shanghai showed that 26.05% of children from migrant families wore glasses with incorrect lenses [12].

Previous studies have shown the prevalence of blindness and visual impairment, and the proportion due to uncorrected or improperly corrected refractive errors. Because of the potential observation bias and recall bias, these studies may provide limited information on the quality of local optometry services. We need a methodology and criteria for establishing quality indicators. In recent years, the unannounced standardized patient (USP) has been increasingly used for healthcare quality measurement in developing countries [13–15]. The USP methodology as the gold standard for quality assessment [16, 17] in clinical practice has the following advantages of being: (a) an objective and direct assessment of care in a real visit; (b) unannounced and thus having no Hawthorne effect (also referred to as the observer effect, in that individuals modify an aspect of their behaviors in response to their awareness of being observed [18]; c) standardized in case presentation and thus providing a natural control for case mix; and d) immediate in terms of recording assessment results and thus having less recall bias. Furthermore, the use of USPs enables us to conduct a randomized controlled trial with multi-arms by creating an experiment condition of the USP case while holding other USP factors constant.

USP encounters were validated as an effective way of measuring reproducibility refractive error within optometry [19]. Sean et al. [6] conducted a cross-sectional survey in Shaanxi, which was the first study to use USPs to assess the quality of eye care in China. Their findings indicated an inaccuracy rate of 25.6% (≥ 1.00D absolute difference) in optometry prescriptions, which was higher than the 18.4% reported in a previous study that did not use standardized patient methods in rural western China [11]. They also found that public hospitals provided poorer quality optometry services compared with private optical shops. Compared with hospitals that generally prescribe rather than dispense spectacles, private optical shops mainly profit from spectacle sales and thus may be incentivized to provide better optometry service to reduce after-sales services for patients with uncomfortable spectacles.

But this USP study still offers areas for improvement. The study used vector dioptric distance (VDD) alone as an outcome indicator for quality. However, VDD has not been validated as a proxy for patients’ refractive tolerance [20], thus, VDD should be used in conjunction with a measure for vision comfort [5, 21]. Otherwise, we need another more reliable indicator, such as optimally prescribed spectacles (or optimal spectacle prescription), for measuring optometry quality (more details in the section on method).

However, those cross-sectional studies only describe the current situation, without continuing to explore the quality improvement of eye care. Along with the promotion of the Healthy China Initiative, eye health policy in the new era has gradually shifted towards high-quality development of eye care. But the change in the policy system is a complex and difficult process, requiring multiple inputs and reforms in various aspects. While the national policy system is undergoing continuous reform, it is beneficial to explore how patients themselves can shape the quality of care during patient-practitioner interactions. Brief verbal intervention (BVI) is an easy and effective method commonly used in primary health services, such as smoking cessation interventions and reducing alcohol intake [22]. In this study, we will use USP to test the effectiveness of BVI in improving eye care quality, especially for optometry services. By utilizing the USP, we are able to vary a specific component (such as a different line used as a form of BVI) across providers while keeping other USP elements constant. As a result, any variations in measurements among the providers can be solely attributed to this particular component.

### Objectives

In summary, the objectives of the study are: (1) to assess the quality of the structure, process, and outcomes of optometry service; (2) to analyze the factors that influence the quality of optometry service; and (3) to assess the effectiveness of patient-based BVI on improving the quality of optometry service.

## Methods

### Study design and setting

The study is designed as a prospective, single-blind, multi-center, randomized controlled trial with four arms – three intervention groups versus a common control group of the participating optometry service providers (OSPs).

The study will be carried out in Guangzhou and Inner Mongolia, China. Guangzhou is the capital city of Guangdong Province, representing a well-developed metropolitan in the south of China. Inner Mongolia’s autonomous region has fewer medical resources, representing relatively underdeveloped land in China. We chose three cities in Inner Mongolia, which are Bayannur (west), Hohhot (central) and Xinganmeng (east). Optometry service providers (OSPs) are considered for inclusion if they meet the criteria defined below. In each location, we will draw a representative sample of eligible OSPs using stratified and simple random sampling.

### Participants and recruitment

OSPs are not informed of participation, thus they will be visited unannounced by USP. We will recruit USPs and train them, implementing interventions in different groups. Figure 1 presents an explicit flow chart of this study.

The study subjects (OSPs and their refraction-ists) must meet the following criteria to be eligible for the study: (1) OSPs in Guangzhou and Inner Mongolia, consisting of general hospitals with ophthalmology department, ophthalmology specialty hospitals or clinics, and optical shops; (2) any personnel providing optometry services, as licensed optometrists and ophthalmologists or not, at the above-mentioned institutions. Exclusion criteria include: (1) providers providing Internet-based services only; (2) providers providing optometry service solely for contact lenses only.

**Fig. 1 Fig1:**
[figure not shown]
Flow chart of the study

The USPs must meet the following criteria to be eligible for the study: (1) people with refractive error profile of interest (myopia or myopia with astigmatism), and good ocular health; (2) fluent native speakers of the primary language of the district; (3) having a good memory. If the USPs meet any of the following criteria, they will not be eligible for the study: (1) having prior refractive eye surgery or had eye surgery within the last three months; (2) having manifest or intermittent strabismus, or amblyopia; (3) people with any ocular or health conditions that can cause variable spectacle prescription.

We will develop the sampling frame of all OSPs who meet our inclusion and exclusion criteria by crawling the data of Gaode Map, the leading map service App with the advantage of capturing both registered and non-registered optical shops in China. We will select the sample of OSPs with stratified and simple random sampling. Likewise, we will recruit USPs by posting part-time job announcements on campus posters and social media, like WeChat, and also through our existing USP network. The USPs will be paid for participation and reimbursed for other related expenses.

At recruitment, all USPs and their companions must sign the informed consent electronically through a web link sent by our emails. We have obtained a waiver for informed consent from the OSPs as the process may compromise the sample representation due to possible participant self-selection. We meet the criteria of consent waiver for the USP studies as stipulated by the medial ethics: (1) data analysis will only be performed at the aggregated level rather than targeting individual participants; (2) de-identification for the participating individuals and institutions will be fully implemented; and (3) services performed on USPs are not critical services where resources must be protected for the real patients [23].

### Sample size calculation

We calculated the sample size based on the proportion of optometry accuracy, which is the primary outcome of this study. According to the previous literature [5], the proportion of optometry accuracy is 44.1% in the control group (receiving usual USP visits), and proportions in the intervention groups (receiving usual USP visits plus BVIs) are supposed to be 66.1% (when assuming the effect size of 0.22). Accounting for multiple comparisons of proportions (the proportion of optometry accuracy) for treatments vs. a control [24], the overall alpha is set to be 0.05, thus a level of significance is 0.0167 (0.05/3) by using Bonferroni adjustments. In this study, we set the power of each test at 0.9, all groups have the same sample size. And finally, a total of 456 USP visits is required, each OSP is corresponded to a USP visit. Considering 5% of dropout and/or missing data, the number of participants adds up to a total of 480 participants. The sample size required for the control group and each of the intervention group is 120 respectively. The sample size calculation was performed using PASS 15 software (NCSS, Kaysville, UT, USA).

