### Statistical analysis plan

Data will be analyzed on an intention-to-treat (ITT) basis to compare primary and secondary outcomes in the originally assigned groups. Baseline characteristics for each group will be descriptively presented using mean (standard deviation, SD) or median (interquartile range, IQR) for continuous variables depending on the distribution, and frequency (percent) for categorical variables.

Primary outcome (optometry accuracy) and secondary outcomes will be analysed using generalized linear models (GLMs). Binomial distribution and identity link function will be used for binary outcomes, Poisson distribution and identity link function will be used for count outcomes, and normal distribution and identity link function will be used for continuous outcomes. Effects (risk differences for binary and count outcomes, and mean differences for continuous outcomes) with corresponding two-sided 95% confidence intervals will be estimated. Missing data will be imputed using multiple imputation in the GLMs.

Sensitivity analysis will be performed by covariate-adjusted analysis using GLMs with baseline characteristics as covariates. Cost-effectiveness analyses will be performed, and cost-effectiveness ratios will be calculated using bootstrapping techniques. Statistical significance will be considered to be present when the P value is < 0.05. Subgroup analyses will be performed, based on the type of service (hospitals and optical shops) and types of practitioners (such as licensed vs. unlicensed practitioners). IBM SPSS (version 20) and SAS (version 9.4, SAS Institute) will be used for all statistical analyses.

Subgroup analyses will be performed, based on type of service (hospitals and optical shops) and types of practitioners (such as licensed vs. unlicensed practitioners).

We expect the number of withdrawals to be low because the intervention is delivered by the USP and the service provider will receive the intervention passively. Additionally, the intervention will be conducted over a brief period of one USP visit thus without post-visit follow-ups. All data will be entered into the REDCap system immediately after the visit. Thus, we expect to have minimum (if any) missing data. A maximum dropout and/or missing data of 5% is considered in our sample size calculation. We will analyze the data according to the ITT principle.

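### The Bonferroni level of 0.0167 used to size the trial is not carried into the analysis section, which tests at P < 0.05; naming Holm there would restore the 5% family-wise error with more power than Bonferroni

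*Protocol article*

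**What the plan says.** In the protocol article, Sample size calculation, the primary outcome is the proportion of accurate prescriptions, and three intervention arms are each compared with one control arm. On error control it says "the overall alpha is set to be 0.05", and then "thus a level of significance is 0.0167 (0.05/3) by using Bonferroni adjustments". On power it says "we set the power of each test at 0.9, all groups have the same sample size". The assumed proportions are 44.1% in the control arm and 66.1% in every intervention arm. The result is 456 visits (114 per arm), raised to 480 (120 per arm) for 5% dropout. The section does not say whether the tests are one-sided or two-sided.

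The Statistical analysis plan section of the same article says of the effect estimates "with corresponding two-sided 95% confidence intervals will be estimated", and of the decision rule "Statistical significance will be considered to be present when the P value is < 0.05". It mentions neither Bonferroni nor any other adjustment for the three comparisons. Bonferroni in the sample size section is the only multiplicity method named in the document.

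**The concern.** The two sections give different decision rules for the same three primary tests. One promises an overall 5% error and divides it by three. The other, which governs the analysis, gives 0.05 without qualification. An analyst who follows the analysis section would test each BVI at 0.05 and lose the error control on which the trial was sized. An analyst who follows the sample size section would use single-step Bonferroni. That is valid, but a procedure with the same error guarantee rejects everything Bonferroni rejects and sometimes more.

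The trial compares three distinct interventions, and its aim is to learn which of them work. Both a false claim for one BVI and a missed effect of another would matter. The sponsor has to add a sentence to reconcile the sections in any case, so it is worth choosing the better procedure.

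**Working it through.** **Inputs (Sample size calculation):** control 0.441; each BVI 0.661; difference 0.22; overall alpha 0.05; three comparisons; power 0.90 per test; equal arms; 5% dropout. Two-sidedness is taken from the intervals in the Statistical analysis plan section.

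**1. The plan's own figure.** With unpooled variance, n per arm = (z_alpha + z_power)² × [p0(1−p0) + p1(1−p1)] / d².

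- Variance sum: 0.441 × 0.559 + 0.661 × 0.339 = 0.2465 + 0.2241 = 0.4706. d² = 0.0484.
- One-sided 0.0167: (2.128 + 1.282)² × 0.4706 / 0.0484 = 113.03, so 114 per arm and 4 × 114 = 456. This matches.
- Two-sided 0.0167: (2.394 + 1.282)² × 0.4706 / 0.0484 = 131.4, so 132 per arm and 528. This does not match.
- With pooled variance, one-sided gives 117 per arm (468) and two-sided gives 136 (544).
- Dropout: 456 / 0.95 = 480. This matches.

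Of the formulas tried, only the one-sided unpooled one returns 456 exactly.

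**2. Family-wise error if the analysis section is followed.** All three comparisons share the control arm, so with equal arms the test statistics have correlation 0.5. Under the global null,

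FWER = 1 − ∫ φ(t) [Φ((c − √0.5·t)/√0.5) − Φ((−c − √0.5·t)/√0.5)]³ dt.

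- c = 1.960 (two-sided 0.05 each): 12.5%. Simulation of the binomial trial at 114 per arm gives 13.2%.
- c = 2.394 (two-sided 0.0167 each): 4.45%. Simulation gives 4.6%.

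**3. Bonferroni against Holm.** Holm compares the smallest P value with 0.05/3 = 0.0167, the next with 0.05/2 = 0.025 and the largest with 0.05, stopping at the first failure. Its first step is the Bonferroni step, so under the global null it has the same error (4.6% simulated), and it can never reject less. Simulated power with two-sided z tests, 114 per arm and the shared control arm simulated:

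| BVIs that work | Power per effective BVI, Bonferroni | Power per effective BVI, Holm |
|---|---|---|
| All three | 83.4% | 90.0% |
| Two | 83.4% | 86.9% |
| One | 83.4% | 83.5% |

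If all three work, power to detect all three is 66% with Bonferroni and 82% with Holm. Power to detect at least one is 96.6% with both.

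**4. The same comparison on the one-sided basis that returns 456.** If all three work, power per test is 90.4% (Bonferroni) against 94.2% (Holm), and power for all three is 79.1% against 89.0%. If one works, both give 90.4%. The ranking therefore does not depend on sidedness.

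**5. Power at two-sided 0.0167 for a BVI that works alone.** It is about 83–85% at 114 per arm and about 85–87% at 120, depending on the variance formula. Reaching 90% needs 132–136 per arm.

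**The case against.** The strongest defence is that nothing in the sample size section is wrong on this point. Bonferroni is a valid, pre-specified choice and yields matching simultaneous intervals directly. Sizing at 0.0167 is also the right conservative basis for a per-test power target, because Holm's first step is at 0.0167 too. Nor does sizing at 0.0167 rule out a Holm analysis on the same number of visits. All of this stands, so the choice of Holm over Bonferroni is an efficiency gain and not the correction of an error.

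It can also be said that the testing procedure may be set out in a separate analysis plan that is not shown, or that the 0.05 threshold was meant for adjusted P values. Either is possible. But the article does not stay silent: it states a threshold and an interval level that, as written, do not agree with its own overall alpha. That is a conflict within the document, not an omitted detail.

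A reader might infer something stronger: that the final tests will be run at 0.0167 and power is thereby given away for nothing. The documents do not support this. Bonferroni appears only in the sizing; taken literally, the analysis section loses no power (about 92–93% per test at two-sided 0.05 with 114 per arm) but loses the error control. A reader might also blame Bonferroni for the gap between 83% and the stated 90%. That gap comes from sidedness: on the one-sided basis that returns 456, Bonferroni delivers 90.4%.

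**Conclusion.** The point holds as a mismatch between two sections, with a better procedure available to close it. The sample size section promises an overall 5% error; the analysis section, followed for each comparison, gives about 13%. Holm restores the 5% and dominates Bonferroni for testing.

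The size of Holm's gain depends on how many BVIs work. At 114 per arm, two-sided, it is 6.6 points per test if all three work at the full 22-point difference, which is the protocol's own planning scenario. It is about 3.5 points if two work and practically nil if one does. The chance of at least one positive finding does not change.

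The figures assume 44.1% against 66.1%, independent visits and normal-approximation tests. Holm does not mend the sizing. The plan's 90% per test is not met at two-sided 0.0167 for a BVI that works alone. That the sizing was one-sided is inferred from the arithmetic and is not stated.

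**What to change.** Add to the Statistical analysis plan section: the three primary comparisons with control are tested with Holm's procedure, comparing the ordered P values with 0.0167, 0.025 and 0.05, at an overall two-sided level of 0.05; Bonferroni simultaneous confidence intervals (each at 1 − 0.05/3, or 98.33%) are reported alongside. Limit the general 0.05 threshold to analyses outside this family.

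Step-down Dunnett is an acceptable option and uses the shared-control correlation. With normal critical values, however, its simulated error was 5.2% at 114 per arm, so Holm is the safer default.

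State the sidedness of the sample size calculation as well, since the Holm sentence does not resolve it. If 90% per test is to hold at two-sided 0.0167, the calculation gives 528–544 visits before dropout instead of 456; otherwise, state the lower power.

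The Holm change costs one sentence and no extra visits. The small downside is that the simultaneous intervals will be slightly wider than the Holm tests imply, so an interval may include zero for a comparison that Holm declares significant. The report should say so in advance.

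### The 456 visits give 90% power only for a one-sided test at 0.0167; two-sided, as the analysis section implies, power is about 85%

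*Protocol article*

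**What the plan says.** The Sample size calculation section gives every input except the sidedness of the test:

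- Control proportion: "the proportion of optometry accuracy is 44.1% in the control group".
- Intervention proportion: 66.1%, a difference of 22 percentage points.
- Level per comparison: "thus a level of significance is 0.0167 (0.05/3) by using Bonferroni adjustments".
- Power and allocation: "we set the power of each test at 0.9, all groups have the same sample size".
- Result: "And finally, a total of 456 USP visits is required". Divided over four equal arms, this is 114 per arm.
- Allowance for loss: "Considering 5% of dropout and/or missing data, the number of participants adds up to a total of 480 participants", or 120 per arm.

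The Statistical analysis plan section analyses accuracy with a binomial GLM and identity link, so the effect is a risk difference, "with corresponding two-sided 95% confidence intervals will be estimated". That is the only statement about sidedness in the article. One-sided testing is not mentioned anywhere.

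**The concern.** Unless a protocol says otherwise, a reader takes a stated power to refer to a two-sided test. Here the two-sided intervals in the analysis section support that reading. Yet 114 per arm looks too small for 44.1% versus 66.1% at a two-sided level of 0.0167 with 90% power. If the figure comes from a one-sided calculation, the protocol claims more sensitivity than the planned inference has.

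This matters most if a comparison turns out null. Each of the three verbal interventions is compared separately with the common control, and a non-significant result would be read against an overstated chance of having detected a 22-point gain. The purpose given under Control group is to find out whether the intervention changes practitioner behaviour. That question has no built-in direction, and a fall in accuracy would also be of interest.

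**Working it through.** **Inputs** (all from Sample size calculation): p₁ = 0.441, p₂ = 0.661, difference d = 0.22, α = 0.05/3 per comparison, power 0.90, equal arms. The normal quantile for 90% power is 1.282.

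**Variance term.** 0.441 × 0.559 + 0.661 × 0.339 = 0.2465 + 0.2241 = 0.4706.

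**Formula (unpooled).** n per arm = (z_α + 1.282)² × 0.4706 / 0.22². The unpooled form matches the planned risk-difference model.

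**Step 1: reproduce the stated figure.** One-sided α = 0.05/3 gives z_α = 2.128.

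- (2.128 + 1.282)² = 11.625
- n = 11.625 × 0.4706 / 0.0484 = 113.03, rounded up to 114
- 4 × 114 = 456, the stated total
- 456 / 0.95 = 480, the stated total after loss

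The match depends on using 0.05/3 unrounded. With 0.0167 the result is 112.98, which rounds up to 113.

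**Step 2: the same inputs, two-sided.** z_α = 2.394.

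- (2.394 + 1.282)² = 13.51
- n = 13.51 × 0.4706 / 0.0484 = 131.35, rounded up to 132, or 528 in total

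**Step 3: other methods at the same level and power.**

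| Method | Per arm | Total |
|---|---|---|
| One-sided, unpooled | 114 | 456 |
| One-sided, pooled | 117 | 468 |
| Two-sided, unpooled | 132 | 528 |
| Two-sided, pooled | 136 | 544 |
| Two-sided, arcsine | 136 | 544 |
| Two-sided, continuity-corrected | 145 | 580 |
| Two-sided, Dunnett critical value 2.349 (pooled) | 133 | 532 |

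No two-sided method comes near 456 at the stated level. The nearest two-sided match is an unadjusted 0.05 test with continuity correction (115 per arm, 460 in total), which contradicts the Bonferroni level on which the section bases its calculation.

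**Step 4: power actually available, two-sided at 0.05/3.** At 114 per arm the standard error is √(0.4706/114) = 0.06425, so d/SE = 3.424 and power = Φ(3.424 − 2.394) = Φ(1.030) = 84.9%. At 120 per arm the standard error is 0.06262, d/SE = 3.513 and power = Φ(1.119) = 86.8%.

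| Evaluable per arm | Unpooled, approximate | Pooled, approximate | Unpooled, exact | Pooled, exact |
|---|---|---|---|---|
| 114 | 84.9% | 83.4% | 85.0% | 83.5% |
| 120 | 86.8% | 85.5% | 85.6% | 85.4% |

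The exact columns come from full enumeration of the two binomial distributions.

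**Step 5: difference detectable with 90% power.** Holding control at 44.1% and solving d / √{[p₁(1−p₁) + (p₁+d)(1−p₁−d)]/n} = 2.394 + 1.282 gives d = 23.5 points at 114 per arm and 22.9 points at 120.

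**Step 6: what 90% two-sided at 22 points would need with 5% loss.** Unpooled: 132/0.95 = 138.9, so 139 per arm (556 in total). Pooled: 136/0.95 = 143.2, so 144 per arm (576 in total).

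**The case against.** The strongest reply is that the 85% joins the level from one section to the sidedness of another. The sample size section does not state the sidedness, and the analysis section attaches the word two-sided to 95% confidence intervals, not to a test at 0.0167. That the tests are two-sided is therefore an inference. The analysis section's own rule is significance at P < 0.05. On that rule, two-sided power at 114 per arm is about 92% to 93%. On a one-sided 0.0167 reading it is 90.3% (unpooled), and the stated objective of improving quality is directional.

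Two further points concern size. Providers who refuse or become unblinded are replaced and little missing data is expected, so the evaluable number may be nearer 120 than 114. The shortfall of about 3 to 5 points at 120 is also modest beside the uncertainty in an assumed 22-point effect.

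Part of this stands. The two-sided reading is inferred, the consequence is moderate, and the design is not endangered. But none of it restores the stated 90%. The 92% to 93% is reached only by giving up the multiplicity control to which the sample size section ties its power. The one-sided reading is not declared and does not fit the two-sided intervals. Full retention still leaves 85% to 87%. If a one-sided test was intended, the protocol would have to say so and reconcile it with the intervals, so the text needs correcting either way.

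**Conclusion.** The point holds. At the stated Bonferroni level, 456 visits correspond to 90% power only for a one-sided test. For the two-sided inference that the protocol indicates, power per comparison is 83% to 85% with 114 evaluable visits per arm and 85% to 87% with 120. The type II error is about 15% instead of 10%, half as large again.

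This rests on two assumptions: that the primary comparisons are two-sided, taken from the confidence intervals, and that the 0.0167 level governs them, as the sample size section says. The accuracy proportions are taken as given. The trial keeps reasonable power, and what is wrong is the figure attached to its primary outcome.

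**What to change.** Keep 480 providers. In Sample size calculation, state that the tests are two-sided and replace the 90% claim with wording such as:

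> With 114 evaluable visits per arm, each two-sided comparison at the 0.0167 level has about 85% power to detect 44.1% versus 66.1%, and 90% power to detect a difference of 23.5 percentage points.

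These are the unpooled figures, which match the risk-difference model; the pooled power at 114 per arm is about 83%. The analysis section's P < 0.05 threshold should be brought into line with the 0.0167 level at the same time, because the corrected sentence describes a test at 0.0167.

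The cost is a sentence of text and a slightly less favourable power figure, with no extra recruitment. Keeping 90% power at 22 points would instead require 556 providers (unpooled) to 576 (pooled) with 5% loss, that is 76 to 96 more than planned. The size of the shortfall does not call for that.
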